# Investigation on the effect of antimicrobial photodynamic therapy as an adjunct for management of deep caries lesions—study protocol for a randomized, parallel groups, controlled clinical trial

**DOI:** 10.1186/s13063-023-07181-8

**Published:** 2023-03-04

**Keywords:** Photodynamic therapy, Dental caries, *Bixa orellana*, LED, aPDT

## Abstract

**Background:**

Alternatively to conventional treatments, chemo-mechanical caries removal agents can be used. A modality of treatment that has been increasing in dentistry is antimicrobial photodynamic therapy (aPDT). *Bixa orellana* is being researched for application in aPDT. This protocol aims to determine the effectiveness of aPDT with *Bixa orellana* extract in deep caries lesions.

**Methods:**

A total of 160 teeth with deep occlusal dental caries will be selected and divided into 4 groups: G1 - control group (Caries removal with a low-speed drill); G2 - Partial Caries Removal with Papacarie™ (Fórmula e Ação, São Paulo, SP, Brazil); G3 - Partial Caries Removal with Papacarie™ and application *Bixa orellana* extract (20%) (Fórmula e Ação, São Paulo, SP, Brazil); G4 - Partial Caries Removal with Papacarie™ and application *Bixa orellana* extract (20%) with LED (Valo Cordless Ultradent®, South Jordan, UT, USA) (aPDT). After treatment, all the teeth will be restored with glass ionomer cement and followed up clinically and radiographically, with evaluations at immediately, 1 week, and 1, 3, 6, and 12 months. Dentin samples before and after treatment will be analyzed microbiologically. The efficacy of treatments will be assessed with microbiological (colony-forming units, before and after carious tissue removal), radiographic (integrity of the periapical area and eventual changes in the radiolucent zones), and clinical examinations (retention of the restorative material in the cavity and occurrence of secondary caries), as well as with the time required for the procedures and the need for anesthesia during the procedures. In case data distribution is normal, analysis of variance (ANOVA) will be used for both the dependent and independent variables. In case the data distribution is not normal, the Friedman test will be used for the dependent variables. For independent variables, the Kruskal-Wallis test will be used.

**Discussion:**

Procedures using aPDT have been developed for the treatment of dental caries, but there are few controlled clinical trials in the literature confirming its efficacy.

**Trial registration:**

This protocol is registered at ClinicalTrials.gov under the number NCT05236205 and it was first posted on 01/21/2022 and last updated on 05/10/2022.

## Administrative information

Note: the numbers in curly brackets in this protocol refer to the SPIRIT checklist item numbers. The order of the items has been modified to group similar items (see http://www.equator-network.org/reporting-guidelines/spirit-2013-statement-defining-standard-protocol-items-for-clinical-trials/).

## Introduction

### Background and rationale {6a}

Antimicrobial photodynamic therapy (aPDT) is a promising new approach that aims to promote the reduction of microorganisms and it can be an innovative treatment to control oral biofilm microorganisms [1, 2]. Among these microorganisms, *Streptococcus mutans (SM)* and lactobacilli are usually present [1, 2]. Furthermore, it has been used in the treatment of dental caries [3]. Many studies have been conducted to confirm the effectiveness of this treatment modality [3–6].

The minimally invasive clinical treatment is considered an approach to the treatment of tooth decay, which acts on detection, diagnosis, interception, and treatment at the microscopic level. The partial removal of dental caries in order to maintain the integrity of the pulp is currently considered the treatment of choice for deep carious lesions, provided that some diagnostic principles are respected [7].

Currently, the treatment of these lesions is done with the removal of carious tissue using burs, hand excavators, or other techniques. Alternatively, chemo-mechanical caries removal agents can be used instead [8]. Papacarie ™ is considered a minimally invasive clinical treatment approach to treating dental caries with proven efficacy [3, 7–10]. It is a papain-based gel employing natural enzymes extracted from papaya husk that promotes the softening of the dentin. The gel acts upon the contaminated dentin and has an effect on local bacteria, as well as being biocompatible and having neutral pH [7]. However, it is necessary to improve its antimicrobial action. Clinical studies conducted to evaluate the antimicrobial potential of Papacarie™ (Fórmula e Ação, São Paulo, SP, Brazil) attribute its efficacy to its physical-chemical properties [8]. Partial caries removal by the Papacarie™ is capable of effectively dissolving the structure of caries-infected dentin through cysteine protease enzymatic action with additional bactericidal and anti-inflammatory properties [10].

This approach has been increasing in dentistry, being associated with antimicrobial photodynamic therapy (aPDT) [4–6]. The use of red/yellowish dyes is being researched for their application in aPDT. *Bixa orellana* is a plant native to Brazil. From its seeds, it is possible to extract a dye, popularly known as “urucum.” This dye has important antioxidant and antimicrobial activities, and recent studies have shown its potential as a photosensitizer in aPDT [3, 6, 11, 12]. Due to its positive characteristics, especially regarding the lack of mutagenic and cytotoxic activity and antimicrobial effect, the *Bixa orellana* extract (Fórmula e Ação, São Paulo, SP, Brazil) could be considered a suitable candidate as a photosensitizer. Using a dye with these characteristics would make aPDT more accessible [6, 13].

There are no controlled clinical trials in the literature that confirm the effectiveness of this type of therapy on deep caries-affected dentin associating Papacarie™ and aPDT with *Bixa orellana* extract, especially in the deep caries lesion. The justification for performing the treatment with Papacarie™ associated with aPDT using the *Bixa orellana* extract is to reduce the risk of pulp exposure in permanent teeth and increase the antimicrobial activity.

### Objectives {7}

#### General objectives

To investigate the use of Papacarie™ and aPDT with *Bixa orellana* extract on the caries-affected dentin of permanent teeth through a controlled clinical trial.

#### Specific objectives

To investigate the efficacy of photodynamic therapy with *Bixa orellana* and Papacarie™ with regard to microbiological (counting of colony-forming units before and after treatments – CFU), radiographic (integrity of the periapical area and eventual changes in the radiolucent zones), and clinical aspects (retention of the restorative material in the cavity and occurrence of secondary caries) (primary objective);To evaluate the antimicrobial effect of aPDT on caries-affected dentin in permanent teeth (secondary objective);To perform a radiographic evaluation of the remaining dentin and radiographic density at 6 evaluation times, over a 12-month period (secondary objective); andTo evaluate the need for local anesthesia during intervention and the degree of pain/discomfort (with a face scale) of children during the different procedures (secondary objective).

#### Hypothesis

Hypothesis (H0): The administration of Papacarie™ and aPDT with *Bixa orellana* extract is not effective in the treatment of caries-affected dentin in permanent teeth.

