### Trial design {8}

This is a study protocol for a randomized (1:1), single-blind (outcome assessors, only), parallel groups, equivalence, one-center, phase 2, controlled clinical trial. Figure 1 shows a schematic diagram and is the Standard Protocol Items: Recommendations for Interventional Trials (SPIRIT) figure.

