Aliquots (100 ml) from each dilution will be sewn onto the surface of agar and spread with the aid of a Drigalski spatula. Undiluted aliquots and aliquots from dilution 10^2^ (100 ml) will be pour-plated on Rogosa SL agar (Difco Laboratories, Detroit, Michigan) for the determination of lactobacilli (LB). The Brucella agar dishes will be incubated in an anaerobic chamber (PLAS by LABS, Lansing, MI) at 37°C for 7 days. The Mitis Salivarius agar and Mitis Salivarius Bacitracin dishes will be incubated in a 10% CO_2_ atmosphere (CO_2_ greenhouse, Shel Lab, mod. 2123, Oregon) at 37°C for 48 h. The dishes containing Rogosa agar will be incubated in a 10% CO_2_ atmosphere at 37°C for 72 h. After incubation, the characteristic colonies in each dish will be counted with the aid of a stereomicroscope at a magnification of 10 times in dilutions with 30 to 300 colonies per dish. All procedures will be performed in duplicate, and the mean of the counts will be calculated. The results will be expressed in colony-forming units (CFU) of SM and LB as well as in proportion of streptococcus (% S/VM), SM group (% SM/VM and lactobacilli (% LB/VM) in relation to the total of viable microorganisms (VM). For SM, the proportion in relation to the total of streptococci (% SM/S) will also be calculated. Immediately after the removal of the carious tissue, samples of the remaining dentin will be taken with a Meyhoefer auricular n° 2 curette and the procedures will be repeated [14].

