### Sample size {14}

The sample size was calculated based on a previous study in the literature [16, 17] (Fig. 2), considering the expected difference and standard deviation and weighting colony-forming units (CFU) of bacteria. For the statistical calculation, paired samples were considered, with α=5% and an 80% test power. The minimum number in this clinical trial was determined to be 34 teeth per group. Therefore, 40 teeth per group will be recruited to compensate for possible dropouts during the experimental period. G*Power 3.1 was used to perform the calculations (Fig. 3).

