## Statistical methods

### Statistical methods for primary and secondary outcomes {20a}

The data will be stored in Excel datasets and analyzed statistically by employing different tests and considering a 5% level of significance. Only the researchers involved in the study will have access to the data, even if the study is discontinued. The results will be submitted to the Shapiro-Wilk test to check for normality. In case data distribution is normal, analysis of variance (ANOVA) will be used for both the dependent and independent variables. In case the data distribution is not normal, the Friedman test will be used for the dependent variables, followed by the Wilcoxon test as post hoc. For independent variables, the Kruskal-Wallis test will be used, followed by the Mann-Whitney test as post hoc. Pearson (for normal data) or Spearman (for non-parametric data) correlation coefficients may be calculated to determine correlations among the variables.

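### The only stated hypothesis names no comparator and no test is tied to it, so a before/after CFU fall in Group 4 could be used to reject it even if the light adds nothing

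*Protocol article*

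**What the plan says.** All references are to the protocol article.

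- **Aim.** The abstract's Background states: "This protocol aims to determine the effectiveness of aPDT with *Bixa orellana* extract in deep caries lesions".
- **Hypothesis.** One null is given, under Objectives {7}: the combination of Papacarie and aPDT with the extract "is not effective in the treatment of caries-affected dentin in permanent teeth". No comparator, endpoint or margin is named.
- **Primary objective.** Specific objectives also treats Papacarie and aPDT as one package. Its microbiological part is "counting of colony-forming units before and after treatments". The antimicrobial effect of aPDT itself is a secondary objective, again without a comparator.
- **Design.** Trial design {8} describes a "randomized (1:1), single-blind (outcome assessors, only), parallel groups, equivalence, one-center, phase 2, controlled clinical trial". Eligibility criteria {10} intends one tooth per child.
- **Sample size {14}.** "paired samples were considered, with α=5% and an 80% test power" gives 34 teeth per group, raised to 40.
- **Tests.** Statistical methods {20a} plans ANOVA if data are normal. Otherwise, "the Friedman test will be used for the dependent variables, followed by the Wilcoxon test as post hoc", with Kruskal-Wallis and then Mann-Whitney for independent data.
- **Comparative intent.** Explanation for the choice of comparators {6b} sets the drill against Papacarie with or without extract and with or without light.

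**The concern.** A null with no comparator can be read as a statement about one arm: counts in Group 4 do not change from before to after treatment. The sample size supports that reading. With parallel arms and one tooth per child, the only pairing available for CFU is before versus after in the same tooth.

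That comparison cannot isolate aPDT. The second sample follows directly on excavation: "Immediately after the removal of the carious tissue, samples of the remaining dentin will be taken". Between the two samples, a Group 4 tooth receives papain gel with extract, curettage of the lateral walls, light and washing. Group 3 receives the same without light. Group 2 receives gel, curettage and washing, without extract or light. A before/after fall in Group 4 therefore shows that all these steps together changed the count.

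At stake is whether a rejected null says anything about aPDT. The trial has the arms needed to answer that question, but the hypothesis does not refer to them.

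**Working it through.** **1. The plan's own figure.** The expected difference and SD are not in the readable text, because the two sample-size figures are not shown. The 34 therefore cannot be reproduced from stated inputs, only solved backwards. For a paired t test with n teeth and standardized mean change dz (mean change divided by the SD of change), power comes from the noncentral t distribution with n − 1 degrees of freedom and noncentrality dz × √n. With alpha 5% and 80% power, n = 34 is returned for:

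- two-sided: dz of about 0.495 to 0.503;
- one-sided: dz of about 0.435 to 0.442.

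Sidedness is not stated. I assume two-sided, with dz = 0.5. The step from 34 to 40 matches 15% loss: 34 / (1 − 0.15) = 40.

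**2. The before/after test when light adds nothing.** Let gel, curettage and washing alone produce a change of size dz, with no contribution from light. At dz = 0.5 the noncentrality is 0.5 × √34 = 2.92 for 34 teeth and 0.5 × √40 = 3.16 for 40. Probability that Group 4's paired test rejects at two-sided 5%:

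| dz from the non-light steps | n = 34 | n = 40 |
|---|---|---|
| 0.3 | 39.7% | 45.7% |
| 0.5 (back-solved) | 80.8% | 86.9% |
| 0.6 | 92.4% | 95.9% |
| 0.7 | 97.7% | 99.1% |
| 0.8 | 99.5% | 99.9% |

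The dz = 0.5 row follows from the sizing: a test with 80% power for a given fall rejects about 80% of the time whatever caused the fall.

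The rank-based fallbacks behave similarly. With Normal changes and dz = 0.495, simulated rejection is about 78–79% (n = 34) and 85% (n = 40) for Wilcoxon. It is about 65% at either size for Friedman with two time points.

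**3. The between-arm test on the same data.** I simulated 20,000 trials per setting, with the same change distribution in Groups 2, 3 and 4. Group 4 versus Group 3, and Group 4 versus Group 2, each rejected 4.7% to 5.3% of the time at every dz tried (0.3 to 1.5). The shared fall cancels.

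**4. Power of the between-arm test.** For n per group and a standardized difference d in change, the noncentrality is d × √(n/2) with 2n − 2 degrees of freedom. At an assumed d = 0.5:

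- n = 34: 0.5 × √17 = 2.06, power 52.9%;
- n = 40: 0.5 × √20 = 2.24, power 59.8%.

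The difference detectable with 80% power is 0.69 SD at 34 per group and 0.63 SD at 40. At d = 0.5, 80% power needs 64 per group, or 64 / 0.85 = 75.3, rounded up to 76, after 15% loss.

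**The case against.** The strongest reply is that the protocol does not adopt a before/after decision rule. It calls the trial parallel-group and controlled, section {6b} says the treatments will be compared, and {20a} plans Kruskal-Wallis with Mann-Whitney, which would include Group 4 versus Group 3. Friedman fits the six radiographic time points better than two CFU samples. The clinical outcome, also primary, has no pre-treatment value, so it cannot be tested before versus after. All of this stands. A reader might infer that the plan is committed to judging aPDT on Group 4's own change; no section says so.

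A reader might also infer that rejection is nearly certain. The documents give no figure for that. It needs dz of about 0.7 to 0.8 or more, while the planning value points to about 0.5, and the Discussion says Papacarie's antibacterial action is not clear-cut in some studies. Tissue removal between the samples makes a larger fall plausible, but that is an assumption.

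A package-versus-drill question is also legitimate, since Group 1 is the named control. Joining Papacarie and aPDT in one hypothesis is thus not an error in itself.

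An analysis plan that is not shown may name a deciding test. But the hypothesis and the power basis are fixed in this document, and as written they leave the within-arm reading open.

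**Conclusion.** The concern holds in a limited form. The only null has no comparator, no planned test is assigned to it, and the stated 80% power belongs to a paired test that cannot separate light from the steps around it. If the null were judged on Group 4's before/after change, an inert light step would still lead to rejection about 81% of the time with 34 teeth and 87% with 40, against about 5% for Group 4 versus Group 3.

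These figures assume Normal changes, a two-sided test, a back-solved dz of about 0.5, and that the non-light steps alone produce that change. At dz = 0.3 the rate is 40–46%; it passes 99% at both sample sizes only once dz is about 0.8. The between-arm power rests on an assumed difference of 0.5 SD. The equivalence label adds to the problem: no margin is stated, and a null of no effectiveness is not an equivalence null.

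**What to change.** 1. **Hypothesis.** Restate the null as no difference between arms in the change in log10 CFU. Use Group 4 versus Group 3 for any claim about aPDT itself, with Group 4 versus Group 2 as support. Use Group 4 versus Group 1 for any claim about the package. The deciding contrast should match the stated objectives.
2. **Statistical methods {20a}.** State that within-arm before/after tests are descriptive and that no effectiveness claim rests on them.
3. **Trial design {8}.** Reconcile the equivalence label with the restated null.
4. **Sample size {14}.** State that 80% power applies to the paired test. Add that 34 to 40 per group gives about 53% to 60% power for a between-arm difference of 0.5 SD, and detects about 0.69 to 0.63 SD with 80% power. Replace the assumed 0.5 SD with the sponsor's own planning value.

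The rewording needs no new data, visits or participants. The cost is that a positive result becomes harder to obtain and the stated power less favourable. Restoring 80% power at 0.5 SD would take 64 analysed teeth per group, so the sponsor must either enlarge the trial or accept and report the lower power.

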### Trial design {8}

This is a study protocol for a randomized (1:1), single-blind (outcome assessors, only), parallel groups, equivalence, one-center, phase 2, controlled clinical trial. Figure 1 shows a schematic diagram and is the Standard Protocol Items: Recommendations for Interventional Trials (SPIRIT) figure.

**Fig. 1 Fig1:**
[figure not shown]
SPIRIT figure as recommended by the 2013 SPIRIT Statement, containing the description of procedures, interventions, assessments, and the study timeline

## Methods: participants, interventions, and outcomes

### Study setting {9}

Participants will be selected from male and female children (with no restrictions regarding race or ethnicity) enrolled for treatment at the pediatric clinic of the dentistry course of Paulo Picanço School of Dentistry (Fortaleza-Ceará, Brazil).

### Eligibility criteria {10}

#### Inclusion criteria

Adequate health with no systemic conditions (ASA 1);Adequate cooperation (scores 1 or 2 in Wright’s modification of Frankl’s behavior scale);Clinically presenting at least 1 permanent molar with an acute, active caries on the dentin not surpassing 2/3 and only involving the occlusal face, with direct view and access as well as no clinical or radiographic signs of pulp involvement. It is not intended to include more than one tooth per participant;Six to 12 years of age;Scores 3 (localized enamel breakdown due to caries with no visible dentine), 4 (underlying dark shadow from dentine), or 5 (distinct cavity with visible dentine) of the International Caries Detection and Assessment System criteria (ICDAS), in the occlusal surface; andThe setting to access these criteria will be during a clinical and radiographic examination, performed in the pediatric clinic of the dentistry course of Paulo Picanço School of Dentistry.

#### Exclusion criteria

Systemic adverse health condition;Uncooperative behavior;Clinically: caries involving enamel, deficient restorations, small carious lesions on dentin with no access for manual scalers, hidden caries, sign or symptom of pulp involvement, clinical impossibility of restoration; andRadiographically: evidence of pulp involvement, carious lesion extending beyond 2/3 of dentin.

### Who will take informed consent? {26a}

The same researcher (who is a dentist) responsible for the procedures will be in charge of approaching the guardians and obtaining the consent form. The researcher will explain all the procedures to be carried out, the purpose of the trial, the risks and benefits of participating in the research, and the fact that the volunteers have complete freedom to choose to participate and/or continue in the research, being able to withdraw at any time, without prejudice. The parents or guardians who agree to allow the minors they are responsible for to participate will sign a written statement of informed consent. They will be given enough time to consider and ask any questions. The children will sign a written assent term, with very simple, clear, and understandable language.

### Additional consent provisions for collection and use of participant data and biological specimens {26b}

Not applicable.

## Interventions

### Explanation for the choice of comparators {6b}

The use of a drill, which is the conventional and most commonly used method, will be compared with the use of Papacarie™ with or without the *Bixa orellana* extract, and with or without the irradiation for aPDT. This study will show which of these treatments will be more efficient with regard to microbiological, radiographic, and clinical aspects. The models, types, and details of all instruments have been detailed upon the first appearance in the text.

### Intervention description {11a}

*Group 1 –* Caries removal with a low-speed drill (control group):Initial periapical radiography (Children's Insight IP-01 Periapical – Carestream, Rochester, Nova York, EUA);Prophylaxis with a toothbrush and fluoride toothpaste (Colgate® Children [name], Nova York, EUA) and fluoride toothpaste (Herjos Prophylactic Paste, Vigodent, Rio de Janeiro, Brazil);Relative isolation with cotton roll (Dental Roller Cotton – Cremer, Santa Catarina, Brazil) and aspirator (Disposable Dental Sucker – SSPlus, Paraná, Brazil);Microbiological sampling with ear curette (Meyhoefer auricular n° 2 curette (ABC Instrumentos Cirúrgicos, São Paulo, Brazil) for standardization of volume of carious tissue;Removal of carious dentin with carbide burs (Carbide Drill No. 6 Spherical CA – Angelus, Paraná, Brazil) and manual instruments (Double Dentin Digger n° 17/18 - Millennium – Golgran, São Paulo, Brazil);Second microbiological sampling with ear curette (Meyhoefer auricular n° 2 curette (ABC Instrumentos Cirúrgicos, São Paulo, Brazil) for standardization of volume of carious tissue;Clinical inspection of texture of the remaining dentin with an exploratory probe (Eighth Exploration Probe – Golgran, São Paulo, Brazil), to check the absence of soft tissue;Restoration with glass ionomer cement (Ketac Molar EasyMix – 3M ESPE); andClinical inspection for signs of infiltration and radiographic follow-up immediately, 1 week, and 1, 3, 6, and 12 months after treatment.

*Group 2 –* Partial removal of carious tissue with the administration of Papacarie™:Initial periapical radiography;Relative isolation with a cotton roll and aspirator;Microbiological sample with otoscope curette to standardize the volume of carious tissue;Application of Papacarie™ (Fórmula e Ação, São Paulo, SP, Brazil) for 5 min, removal of carious tissue around lateral walls of the cavity with a noncutting curette and no removal of carious tissue on pulp floor (partial removal) [10];Washing of the cavity with water and drying with absorbent paper;Second microbiological sampling;Clinical inspection of texture of the remaining dentin with an exploratory probe, to check the absence of soft tissue;Restoration with glass ionomer cement (Ketac Molar EasyMIx 3M ESPE); andClinical inspection for signs of infiltration and radiographic follow-up immediately, 1 week, and 1, 3, 6, and 12 months after treatment.

*Group 3 –* Partial removal of carious tissue with the administration of Papacarie™ and application of *Bixa orellana* extract (20% - seed extract diluted in mineral oil):Initial periapical radiography;Relative isolation with a cotton roll and aspirator;Microbiological sample with otoscope curette to standardize the volume of carious tissue;Application of Papacarie™ with *Bixa orellana* extract (20%) (Fórmula e Ação, São Paulo, SP, Brazil) for 5 min, removal of carious tissue around lateral walls of the cavity with a noncutting curette and no removal of carious tissue on pulp floor (partial removal) [10];Washing of the cavity with water and drying with absorbent paper;Second microbiological sample of remaining dentin with curette;Clinical inspection of texture of the remaining dentin with an exploratory probe, to check the absence of soft tissue;Restoration with glass ionomer cement (Ketac Molar EasyMIx 3M ESPE); andClinical inspection for signs of infiltration and radiographic follow-up immediately, 1 week, and 1, 3, 6, and 12 months after treatment.

*Group 4 –* Partial removal of carious tissue with the administration of Papacarie™, application of *Bixa orellana* extract (20%) and LED (aPDT):Initial periapical radiography;Relative isolation with a cotton roll and aspirator;Microbiological sample with otoscope curette to standardize the volume of carious tissue;Application of Papacarie™ with *Bixa orellana* extract (20%) for 5 min and the light-emitting diode (LED) light curing device (Valo Cordless Ultradent®, South Jordan, UT, USA) an office appliance, with a coupled radiometer, and a spectrum of 440–480 nm will be used. Both the volunteer to be treated and the professional will be using specific eye protection glasses. The active end of the LED will be coated with clear disposable plastic (PVC), thus avoiding cross-contamination. Removal of carious tissue around lateral walls of the cavity with a noncutting curette and no removal of carious tissue on pulp floor (partial removal) [10–12];Irradiation of dental tissue for 1 min on a single point;Washing of the cavity with water and drying with absorbent paper;Second microbiological sample of remaining dentin with curette;Clinical inspection of texture of the remaining dentin with an exploratory probe, to check the absence of soft tissue;Restoration with glass ionomer cement (Ketac Molar EasyMIx 3M ESPE); andClinical inspection for signs of infiltration and radiographic follow-up immediately, 1 week, and 1, 3, 6, and 12 months after treatment.

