### Outcomes {12}

For the treatment of caries lesions to be considered successful, it should be able to remove infected tissue and microorganisms in a sufficient amount, so that, in the control session, the teeth that were once infected do not show any signs of remaining infected tissue beneath the restorative material. Consequently, the microbiological evaluation had been chosen as the primary outcome. However, factors such as the radiological exam and the clinical aspects are also important for the control section, to show the presence or lack of success. Therefore, the microbiological, radiographic, and clinical evaluations should be considered as primary outcomes.

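### Group 1 alone has prophylaxis before the first dentin sample and Groups 2–4 alone have a rinse and dry before the second, so sampling conditions confound the control-versus-test CFU contrast

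*Protocol article*

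**What the plan says.** Intervention description {11a} gives a step list for each arm.

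- **Before the first sample.** Group 1 has a radiograph, then "Prophylaxis with a toothbrush and fluoride toothpaste" together with a prophylactic paste, then isolation, then the sample. The lists for Groups 2, 3 and 4 run "Initial periapical radiography;Relative isolation with a cotton roll and aspirator;Microbiological sample with otoscope curette to standardize the volume of carious tissue", with no prophylaxis.
- **Before the second sample.** In Group 1 the step after burs and hand instruments is "Second microbiological sampling with ear curette". Group 2 has "Washing of the cavity with water and drying with absorbent paper;Second microbiological sampling". Groups 3 and 4 have "Washing of the cavity with water and drying with absorbent paper;Second microbiological sample of remaining dentin with curette", in Group 4 after irradiation.

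The Microbiological evaluation section standardises the curette and the laboratory work and places the second sample directly after caries removal. It states no cleaning step common to the arms before either sample.

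Outcomes {12} says that "the microbiological evaluation had been chosen as the primary outcome", then adds the radiographic and clinical evaluations as primary outcomes too. Sample size {14} is built on CFU.

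**The concern.** A before-and-after count compares arms fairly only if both samples are taken in the same way in each arm. Here two preparatory steps differ, and each differs between the drill control and all three Papacarie arms. Cleaning the tooth with paste could lower the Group 1 starting count and so shrink its apparent reduction. Rinsing the cavity could lower the second count in Groups 2–4 and so enlarge theirs.

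The usual safeguards do not help. The steps come after allocation and follow the arm's own list, so randomisation does not balance them. Blinded laboratory reading cannot undo a difference made before the sample reaches the tube. Adjusting for the first count does not repair a first count that itself depends on the arm.

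At stake is the reading of any CFU difference between the drill and the Papacarie arms, the conventional comparator against which the test treatments are judged.

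**Working it through.** **1. The lists side by side**

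| Step | Group 1 | Group 2 | Group 3 | Group 4 |
|---|---|---|---|---|
| Radiograph before first sample | yes | yes | yes | yes |
| Prophylaxis before first sample | **yes** | no | no | no |
| Isolation before first sample | yes | yes | yes | yes |
| Rinse and dry before second sample | **no** | yes | yes | yes |

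The two rows that differ both split Group 1 from Groups 2–4. Within Groups 2–4 the rows are identical.

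**2. Is it shorthand?** The choice-of-comparators section says that "The models, types, and details of all instruments have been detailed upon the first appearance in the text". That defers instrument details, not procedural steps. The later lists drop brand names but restate radiograph, isolation, sampling, inspection, restoration and follow-up. Prophylaxis is the one preparatory step not restated. Abbreviation after first mention also cannot explain the rinse, which is missing from the first list and present in the three later ones.

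**3. Consistency with the outcome section.** Sampling directly after caries removal fits Group 1's list. In Groups 2–4 a rinse and dry come between. These passages need reconciling whatever the size of the effect.

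**4. How the difference enters the contrast.** Write the log10 reduction as R = log10(first count) − log10(second count). Let b be the amount by which prophylaxis lowers Group 1's first count, and w the amount by which rinsing lowers the second count in Groups 2–4. Then

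observed difference in R (test − Group 1) = treatment difference + b + w.

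A comparison of second counts alone drops b but keeps w. If b = w = 0 there is no distortion. The documents give no value for either.

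**5. The plan's own figure.** The text gives 34 teeth per group (paired samples, α = 5%, power 80%), raised to 40. The effect size is not in the text, and the two sample-size figures are not shown, so 34 cannot be reproduced from stated inputs. A two-sided paired t-test with an assumed standardised difference of 0.50 gives 34, and 34/0.85 = 40 corresponds to 15% dropout. The point here does not alter that number; 34 and 40 serve only as arm sizes below.

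**6. Illustration with an assumed shift.** Take a two-sample t-test of Group 1 against one test arm, two-sided 5%, n per arm, no true treatment difference, and a procedural shift of δ standard deviations in the CFU change. The noncentrality is δ√(n/2) with 2n − 2 degrees of freedom. For δ = 0.25 it is 0.25 × √17 = 1.03 at n = 34 and 0.25 × √20 = 1.12 at n = 40.

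| Assumed δ | Chance of significance, n = 34 | n = 40 |
|---|---|---|
| 0 | 5.0% | 5.0% |
| 0.10 | 6.9% | 7.3% |
| 0.25 | 17.4% | 19.7% |
| 0.50 | 52.9% | 59.8% |

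The δ values are assumptions, and zero belongs in the range.

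**The case against.** The strongest reply is that a procedural difference is not yet a bias.

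- **The sample is scooped dentin, not a surface swab.** Brushing may change its count little or not at all. This stands: b may be near zero.
- **The rinse may belong to the test procedure.** Groups 2–4 receive a gel, and Groups 3 and 4 also an extract in mineral oil; rinsing may serve to clear it. The documents give no reason, but this is plausible. It would explain the difference without making Group 1's unrinsed sample comparable. It does mean that a declared, justified difference is an acceptable way to reconcile the lists.
- **Net direction is open.** Group 1 removes carious dentin with burs, while Groups 2–4 leave it on the pulpal floor. The second samples may come from different tissue, which could push the other way. This stands.
- **Scope is limited.** The contrasts that isolate the extract (Group 3 versus 2) and the light (Group 4 versus 3) share the same sampling steps. The radiographic and clinical outcomes do not use these samples. The statistical methods do not fix a change score, and proportions of viable organisms would be less sensitive to non-selective removal. All of this stands, although a comparison of second counts still carries the rinse difference.
- **The article is condensed, and prophylaxis may have been dropped in writing.** Possible, but as written the arms differ, and nothing in the document equalises them.

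A reader might go further and attach a size. Assuming that prophylaxis removes 50% to 90% of organisms gives −log10(0.5) = 0.30 to −log10(0.1) = 1.0. Adding 0.30 for a rinse that removes half gives about 0.6 to 1.3 log10 against the drill. The documents do not support this: the percentages are invented, the range excludes zero, and loss at a surface is not loss from a scooped volume. Nor may unrinsed debris in Group 1 and rinsing in Groups 2–4 be counted as two effects; they are one difference seen from both sides.

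**Conclusion.** The point holds as a confounded contrast, not as a demonstrated bias. As listed, sampling conditions for a primary outcome differ exactly between Group 1 and Groups 2–4, and the section on microbiological evaluation does not agree with the lists for Groups 2–4 on when the second sample is taken. Each step could plausibly make the reduction look larger in the test arms, but neither size nor net direction can be derived from the documents. The rise in false positives to about 17–20% rests wholly on an assumed shift of 0.25 SD. Contrasts among Groups 2, 3 and 4 stand. The conclusion assumes that the lists are followed as written; if all arms in fact receive the same steps, the fault is in the wording only.

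**What to change.** Reconcile the four lists in Intervention description {11a} with the Microbiological evaluation section. The steps before the first sample, and those between the end of caries removal or irradiation and the second sample, should be the same in all four arms. Which version is used is for the investigators to decide.

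Where a step must differ by arm, for instance to clear the gel, state the difference and the reason. Recruitment was planned from 30 May 2022 to 30 April 2023 and the article appeared on 4 March 2023, so children may already have been treated under the differing lists. In either case, declare the difference when reporting Group 1 against the other arms, and rest the antimicrobial claim on the comparisons among Groups 2, 3 and 4.

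The cost is a wording amendment and about a minute of chair time per child. If the investigators choose to extend prophylaxis, three arms of 40 (3 × 40 = 120 teeth) would also need minor consumables. The fallback costs more in interpretation: the trial could then say less about CFU against the drill.
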